## Abstract

**Background:**

Patients with local gastric cancer experience a decline of Health-related quality of life (HRQOL) during adjuvant chemotherapy following gastrectomy. Our previous pilot study has indicated the potential of acupuncture to improve HRQOL and control cancer-related symptoms burden. This full-scale trial will focus on confirming the effect of acupuncture for patients with gastric cancer.

**Methods:**

A multicenter, open-label, three-arm randomized controlled trial with 249 patients will be conducted in China. Patients will be randomly assigned, in a ratio of 1:1:1, to receive high-dose acupuncture (HA, 7 times each chemo-cycle for 3 cycles), low-dose acupuncture (LA, 3 times each chemo-cycle for 3 cycles), or no acupuncture. The acupoints prescription consisted of bilateral ST36, PC6, SP4, DU20, EX-HN3, and selected Back-*shu* points. Patients-reported Functional Assessment of Cancer Therapy-Gastric (FACT-Ga) and modified Edmonton Symptom Assessment Scale (mESAS) during the therapy will be recorded. Area under curve (AUC, 21 days/cycle × 3 cycles) and average trajectory of FACT-Ga and mESAS will be calculated. The primary outcome will be the differences in AUC of the FACT-Ga Trial Outcome Index (TOI) between HA and LA versus control groups. Secondary outcomes include AUCs and average trajectory of other FACT-Ga subscales and mESAS scores.

**Discussion:**

This study aims to assess the effect of acupuncture and to compare the difference between LA and HA groups on HRQOL and symptom burden controlling in gastric cancer patients by an adequately powered trial.

**Trial registration:**

This study was approved by the Ethics Committee of the Guangdong Provincial Hospital of Traditional Chinese Medicine (approval number: BF2018-118) with registration at ClinicalTrials.gov (identifier: NCT04360577).

**Supplementary Information:**

The online version contains supplementary material available at 10.1186/s12955-023-02135-9.

## Background

Gastric cancer, the fifth most frequently diagnosed cancer and the third leading cause of cancer-related deaths in the world, still constitute a major global health problem, especially in China [1, 2]. Radical resection and postoperative adjuvant chemotherapy are possible ways to cure gastric cancer [3]. However, various symptoms caused by surgery and adjuvant chemotherapy [4, 5] seriously affect the health-related quality of life (HRQOL) and even lead to the interruption of chemotherapy, which increases the risk of tumor recurrence. Although numerous studies showed the impact of surgical technique on the long-term HRQOL [6–8], few studies showed the effect for the short-term HRQOL, especially within the first 3 months after surgery. While the most serious decline of HRQOL often happens within the first 3 months, with nausea, early satiety, reflux, and pain as the most common symptoms [9–11]. Thus, improving HRQOL during the period of adjuvant chemotherapy with an effective intervention has important clinical significance.

Acupuncture is the most widely used traditional and complementary medicine [12] and has been proven to be effective in reducing gastrectomy and chemotherapy-related symptoms by plenty of clinical practice and trials [13–18]. Some clinical practice guidelines and studies recommended acupuncture for cancer-related fatigue [19], cancer pain [20–22], nausea, vomiting [23], chemotherapy-induced peripheral neuropathy [24], hot flashes, and insomnia [25].

However, on the one hand, there are few large-sample randomized control trials or meta-studies on acupuncture improving the overall HRQOL of patients during chemotherapy in gastric cancer. On the other hand, the dosage of acupuncture, such as the number of treatment session, varies in different studies and impact the therapeutic effect [26].In the investigator’s pilot study (NCT 03753399), we presented preliminary evidence that acupuncture was associated with promising effects in improving HRQOL during adjuvant chemotherapy in gastric cancer patients, and showed a difference in the improvement of some symptoms, such as anxiety and depression, between the low-dose acupuncture group and the high-dose acupuncture group [27]. Therefore, studies with a larger sample size are needed to clarify the effect and optimal dose of acupuncture intervention to improve HRQOL of patients with adjuvant chemotherapy after radical gastrectomy.

In this study, we aim to design a multicenter, open-label, three-arm randomized controlled trial to fully assess the effect of acupuncture for HRQOL and symptoms with gastric cancer undergoing adjuvant chemotherapy (Aim 1) and compare the difference between low dose (LA) and high dose acupuncture (HA) groups (Aim 2).

## Methods

The EAGER study, acupuncture for improving the quality of life and symptoms in patients with gastric cancer undergoing adjuvant chemotherapy, follows the Helsinki Declaration and has been approved by the Ethics Committee of the Guangdong Provincial Hospital of Traditional Chinese Medicine (approval number: BF2018-118) with registration at ClinicalTrials.gov (identifier: NCT04360577) before the first participant enrollment. We followed the Standard Protocol Items: Recommendations for Interventional Trials [28] guideline for the reporting of the study protocol.

### Study design

A multi-center, three-arm, open-label randomized controlled trial will be conducted at 11 hospitals in China, including Guangdong Provincial Hospital of Traditional Chinese Medicine, the First Affiliated hospital of Sun Yat-sen University, Affiliated Hospital of Nanjing University of Traditional Chinese Medicine, the Sixth Affiliated Hospital of Sun Yat-sen University, Zhujiang Hospital of Southern Medical University, Guangdong Provincial People’s Hospital, Affiliated Cancer Hospital & Institute of Guangzhou Medical University, the First Affiliated Hospital of Guangzhou Medical University, the Fifth Affiliated Hospital of Sun Yat-Sen University, Foshan First People’s Hospital and Yuebei People’s Hospital. Participants will be recruited from the inpatient and outpatient departments of oncology and surgery. Eligible and consented patients will be randomly assigned, to receive high-dose acupuncture, low-dose acupuncture, or usual cancer with no acupuncture during the first 3 cycles of adjuvant chemotherapy after resection. Participants will be assessed at baseline and during the 3 cycles of chemotherapy (21 days for one cycle) post interventions. The design of the trial is outlined in Fig. 1.

**Fig. 1 Fig1:**
[figure not shown]
Trial procedure flowchart

### Participants

Patients meeting the following criteria are eligible: (1) pathologically diagnosed with gastric cancer or esophagogastric junction cancer after R0 resection and D2 lymph node dissection; (2) pathological stage II or stage III; (3) without tumor recurrence confirmed by image examination; (4) no chemotherapy after surgery, planning to accept at least 3 cycles of adjuvant chemotherapy; (5) age:18 ~ 75 years old; (6) ECOG score ≤ 2; (7) normal organ function, including (7.1) bone marrow function: absolute neutrophil count (ANC) ≥ 1.5 × 10e9/L, platelet (PLT) ≥ 100 × 10e9/ L, hemoglobin (Hb) ≥ 90 g/L; (7.2) kidney function: Serum creatinine (Scr) ≤ 1.5 mg/dl(133µmol/L), or creatinine clearance rate (Ccr) ≥ 60ml/min; (7.3) liver function: total bilirubin (TB) ≤ 1.5×upper limit of normal value (ULN), alanine transaminase (ALT) ≤ 2.5×ULN, aspartate transaminase (AST) ≤ 2.5×ULN; (8) can understand the study well and finish the questionnaires in this study;(9) with the written informed consent. Participants will be excluded if they meet any of the following criteria: (1) cannot finish the baseline assessment; (2) needle phobia; (3) currently diagnosed with a psychiatric disorder (e.g., severe depression, obsessive-compulsive disorder, or schizophrenia); (4) history of autoimmune diseases, hematological diseases or organ transplantation, or long term use of hormones or immunosuppressors; (5) implanted with heart pacemaker; (6) has accepted neoadjuvant radiotherapy before surgery; (7) planning to accept adjuvant radiotherapy after surgery; (8) with active infection; (9) acupuncture treatment within the previous 6 weeks; (10) pregnant or lactating women.

Research staff will screen eligible patients through physical examination and clinical tests. Eligible participants will be required to sign a consent form before enrolment and their information will remain confidential.

### Randomization

Patients will be randomly assigned to the HA group, LA group, and control group (1:1:1), using the central randomization system, allowing for full allocation concealment, provided by the Clinical Trial Management System of Xiyuan Hospital, China Academy of Chinese Medical Sciences (CACS). Random assignment will be stratified by resection extent (total/ proximal or distal gastrectomy) and neoadjuvant chemotherapy status (yes or no). An Electronic Data Capture (EDC) system provided by Xiyuan Hospital CACS will be used for research data management. The study coordinator at each site will ensure that the informed consent form has been obtained from each participant before randomization.

### Interventions

#### Chemotherapy

All participants will be treated with adjuvant chemotherapy with the CapeOx or SOX regimen. The CapeOx regimen consisted of 130 mg/m^2^ of oxaliplatin intravenously on the first day and 1000 mg/m^2^ of capecitabine twice daily for 14 consecutive days, every 21 days. The SOX regimen consisted of 130 mg/m^2^ of oxaliplatin intravenously on the first day and S-1 twice daily for 14 consecutive days, every 21 days. The dose of S-1 will also be calculated according to body surface area (BSA): BSA < 1.25m^2^, 80 mg/day; 1.25m^2^ ≤ BSA < 1.5m^2^, 100 mg/day; BSA > 1.5m^2^, 120 mg/day.

#### Selection of acupuncture points

The acupoints prescription has been developed based on the principles of Traditional Chinese Medicine (TCM) theory [29], literature evidence [30–33] and our clinical experience. It takes into account the gastrointestinal symptoms that are commonly experienced by gastric cancer patients undergoing chemotherapy after gastrectomy [9]. The acupuncture protocol including standard points and individualized points were proven feasible and acceptable to patients in the pilot trial. Standard points consist of bilateral Zusanli (ST 36), bilateral Neiguan (PC 6), bilateral Gongsun (SP 4), Baihui (DU 20), and Yintang (EX-HN3), The individualized points consist of several Back-*shu* points in the bladder meridian according to the meridian diagnosis of traditional Chinese medicine [27, 34]. Full information about the selection of Back-*shu* points is presented in the online supplementary appendix1. The total number of acupoints included is generally about 12 [27].

#### Methods of acupuncture in HA group and LA group

Patients will be in sitting, prone, or in a lateral position to accept acupuncture treatment. Sterile, disposable, stainless steel acupuncture needles (25 or 40 mm and 0.25 mm gauge; Hanyi Medical Instrument Co., Ltd, Beijing) will be gently inserted into acupuncture points. For ST36, PC6, and SP4, needles will be inserted perpendicular to a depth of approximately 10-30 mm from the skin surface. For DU20, EX-HN3, and Back-*shu* points, needles will be inserted obliquely 10-15 mm deep at an angle of 30 degrees to skin. Lifting and thrusting the needles to obtain the sensation known as “*De qi*”, a sense of soreness, warmth, tingling, or heaviness reported by patients suggested effective needling. An electric stimulator (G6805-1 EA apparatus; Xinsheng Industrial Co., Ltd, Qingdao, China) will be connected to the needle handles at bilateral ST36 and PC6 with a 2-HZ continuous wave, and the intensity of electric current will be increased up to a level that patient can perceive and tolerate. All needles will be retained for 20 min. All acupuncturists will be licensed with more than 3 years of clinical experience and receive training on the specific protocol.

Patients in the HA group will accept acupuncture treatment three times in the first week, and then twice a week in the next two weeks during each cycle of chemotherapy (21 days for 1 cycle) for three cycles, namely a total of 21 times acupuncture sessions; those in the LA group will take once a week for three cycles, namely a total of 9 times acupuncture sessions.

#### Methods of usual care in control group

Patients in the control group will only receive usual care according to NCCN clinical practice guidelines in oncology–Antiemesis [23] without acupuncture treatment. After the trial, they will receive the low-dose acupuncture treatment mentioned above for 3 cycles of chemotherapy for the sake of compensation according to their will.

#### Relevant concomitant care and interventions

In principle, all participants will not be given other traditional Chinese medicine therapies, such as Chinese herbs, moxibustion, and acupuncture apart from the study protocol. Receipt of any intervention outside the study protocol should be documented on case record form in detail.

### Outcomes

#### Primary outcome

The primary outcome will be the area under curve (AUC) of Functional Assessment of Cancer Therapy – Gastric(FACT-Ga) scale Trial Outcome Index (TOI) during the 3 cycles of chemotherapy.

#### Secondary outcomes

The secondary outcomes consist mainly of 7 indicators. **(1)** Average trajectory of FACT-Ga TOI over time; **(2)** Total AUC of FACT-Ga Scoring; **(3)** Average trajectory of FACT-Ga Scoring over time; **(4)** Total AUC of Gastric cancer subscale (GaCS) of FACT-Ga; **(5)** Average trajectory of GaCS of FACT-Ga; **(6)** Total AUC of Modified Edmonton Symptom Assessment Scale (mESAS); **(7)** Average trajectory of mESAS.

FACT-Ga has been widely used for the assessment of gastric cancer patients as a well-validated HRQOL instrument (https://www.facit.org/measures/FACT-Ga*)* [35, 36]. It contains four domains, physical well being (PWB) subscale, social/family well being (SWB) subscale, emotional well being (EWB) subscale, and functional well being (FWB) subscale that consists of 27 general HRQOL questions, plus a 19-item gastric cancer subscale, Gastric cancer subscale (GaCS). This is a symbol digital modality test in which the patient reports the intensity of related symptoms on a scale of 0 to 4. The higher scores are considered to be related to a better quality of life. The total score ranges between 0 and 184. FACT-Ga TOI is composed of PWB subscale, FWB subscale, and GaCS subscale of the FACT-Ga Scoring. The range of FACT-Ga TOI is 0-132. The higher score, the better quality of life. FACT-GA for each patient will be recorded at baseline and once a week during the 3 cycles of chemotherapy (21 days for one cycle).

ESAS is a questionnaire widespread used for symptom assessment in cancer patients [37–39]. It was composed of 10 items with a score range of 0–10 for each item, including pain, tiredness, nausea, depression, anxiety, drowsiness, appetite, wellbeing, shortness of breath, and others. ESAS was then modified in 2015 [40], with additional symptoms of constipation and sleep. The higher the score, the worse the symptom is. According to the data of our pilot study, a significant number of patients reported constipation and difficult sleeping, so we used a modified version of ESAS. mESAS scoring for each patient will be recorded every day in the first week, and then once a week in the next 2 weeks during the 3 cycles of chemotherapy (21 days for 1 cycle).

According to our pilot trial, the effect of EA should persist throughout the whole phase of the intervention, rather than at any specific time point [27]. Therefore, the standardized area under curve (AUC, 21days/cycle×3 cycles), calculated by linear interpolation, will be used to reflect the repeated measures of HRQOL (FACT-Ga) and symptom burden (mESAS) during the intervention period [41, 42]. Furthermore, we hypothesized that the effect of EA will be mainly reflected on the TOI scores, which regards more with gastric cancer.

The other pre-specified outcomes include blood test indexes (concentration of circulating myeloid-derived suppressor cells, concentration of circulating Treg cells, and the number of circulating tumor cells), the incidence of treatment-emergent adverse events defined as any adverse events happened after randomization. The severity is validated using national cancer institute common terminology criteria for adverse events (NCI-CTCAE) V4.

The outcome assessments will be performed by outcome assessors at the inpatient department of each participating site. All the outcome assessors will be trained in conducting interviews and performing measurements before the study begins and will follow a standard protocol. The schedule of measurements is presented in Table 1.

**Table 1 Tab1:** Measurements to be taken at each point in the trial

Period		Screening	1st cycle	2nd cycle	3rd cycle	4-6th cycle
Timeline		D-21-0	D1-21	D1-21	D1-21	
**Enrolment**		**×**				

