### Sample size

In our pilot trial, the total AUCs of FACT-Ga TOI during the 3 cycles of chemotherapy were 5402 and 4780 in the acupuncture and control groups, respectively, with a standardized derivation of 1109 [27]. Thus, a total of 62 participants will be needed in each arm to detect a significant difference between the control group and either LA or HA group, with an α of 0.025 and a power of 80%. Considering the total dropout rate of 22.41% in our pilot study and eliminating the impact of COVID-19 epidemics, we plan to enroll a total of 249 patients to allow a dropout rate of 25%.

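### FACT-Ga is scheduled only inside chemotherapy cycles 1-3, so weeks lost to an early stop of chemotherapy would most likely enter the primary AUC as the patient's worst score instead of being observed

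*Protocol article*

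**What the plan says.** All references are to the Protocol article.

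- **Endpoint.** Under Primary outcome, the endpoint is the AUC of the FACT-Ga "scale Trial Outcome Index (TOI) during the 3 cycles of chemotherapy". The paragraph that explains the AUC, after the secondary outcomes, calls it "the standardized area under curve (AUC, 21days/cycle×3 cycles), calculated by linear interpolation". On the scale itself, "The range of FACT-Ga TOI is 0-132", and higher is better.
- **Schedule.** "FACT-GA for each patient will be recorded at baseline and once a week during the 3 cycles of chemotherapy". Table 1 agrees: FACT-Ga is marked only under cycles 1, 2 and 3, each with its own days 1 to 21, and not under cycles 4-6.
- **Name of the AUC.** It is *standardized* in the explanatory paragraph, without a definition. Elsewhere it is a total: the secondary outcomes list "Total AUC of FACT-Ga Scoring", and Sample size reports that "the total AUCs of FACT-Ga TOI during the 3 cycles of chemotherapy were 5402 and 4780" in the pilot's acupuncture and control groups.
- **Interruption of chemotherapy.** The Background says that symptoms of surgery and chemotherapy can "even lead to the interruption of chemotherapy".
- **Missing data.** Under Statistical analysis, missing values are filled by worst observation carried forward (WOCF) to obtain the AUC. The full analysis set drops patients who have baseline data only, so a patient with some later data stays in. The per-protocol set requires at least three cycles of chemotherapy.

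**The concern.** The window of the primary endpoint and the collection of its data both run on the chemotherapy clock. Stopping or delaying chemotherapy is a post-randomisation event, and by the protocol's own reasoning it can follow from the symptoms that acupuncture is meant to relieve. It may therefore differ between arms.

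For a patient who stops early, the schedule produces no more FACT-Ga, yet the patient remains in the full analysis set. The rest of the AUC then depends on an imputation rule. For a patient whose next cycle is late, the weeks of delay have no clear place in the AUC, although they may be weeks in which the patient is unwell.

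At stake are avoidable missing data in the primary endpoint and a possible bias in the comparison of arms. The per-protocol analysis cannot reveal the problem, because it excludes everyone who received fewer than three cycles.

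**Working it through.** **Inputs** (Sample size, Outcomes, Statistical analysis): pilot mean AUCs 5402 and 4780; SD 1109; alpha 0.025, two-sided; power 80%; dropout 25%; cycle length 21 days; three cycles; TOI range 0 to 132.

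**1. The plan's own figure.** The difference is 5402 − 4780 = 622.

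- Normal approximation: n per arm = 2 × (2.241 + 0.842)² × (1109/622)² ≈ 60.4, so 61.
- The t-based solution is 61.7, so 62, with power 80.2%.
- With dropout: 62/0.75 = 82.7, so 83 per arm, and 3 × 83 = 249.

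The stated 62 and 249 reproduce.

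**2. Scale of the AUC.** The nominal window is 3 × 21 = 63 days, and the maximum AUC is 132 × 63 = 8316. The pilot values give 4780/63 = 75.9 and 5402/63 = 85.7, which are plausible mean TOI scores. The AUC is thus in score-days, and the pilot figures fit a 63-day base.

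**3. Early stop, one cycle lost.** Suppose chemotherapy ends after cycle 2 and the 21 unassessed days enter at the patient's worst score. Relative to 21 days at the patient's own mean:

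loss in AUC = 21 × (mean − worst)

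| Worst score below the patient's mean (assumed) | Loss in that patient's AUC | Share of 622 |
|---|---|---|
| 5 points | 21 × 5 = 105 | 17% |
| 10 points | 21 × 10 = 210 | 34% |
| 20 points | 21 × 20 = 420 | 68% |

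Interpolation between the last observed and the first imputed value softens this slightly. Two lost cycles would double it.

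**4. From patient to arm.** These are losses per affected patient. The effect on the comparison depends on how stopping differs between arms, and the documents give no figure. As an assumption, take an imbalance of 10 to 20 percentage points. The arm difference then moves by between 0.10 × 105 = 10.5 and 0.20 × 420 = 84 units, which is 2% to 14% of 622. More stopping among controls would enlarge the apparent benefit of acupuncture. More stopping under acupuncture would shrink it.

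**5. Delayed cycle.** There are two readings.

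- *Fixed 63-day base on cycle days 1 to 21:* a delay adds nothing to the AUC, and the delay weeks are left out.
- *Actual elapsed time:* a 7-day delay adds 7 × 75.9 = 531 (control level) to 7 × 85.7 = 600 (acupuncture level), or 85% to 96% of 622, to a score where higher means better.

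The first reading fits the text better: 21 days per cycle times three, and days 1 to 21 of each cycle in Table 1. The second is not excluded, because *standardized* is undefined and the AUC is also called a total.

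**The case against.** **Delay rules and AUC computation belong to the full protocol or SAP.** This is fair for the handling of delays, and their absence from an article is no finding. The point rests on what is stated: FACT-Ga is collected within cycles 1-3. An analysis plan written later cannot recover questionnaires that the schedule never asked for.

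**A reader might infer that a late cycle inflates the AUC by 531 to 600 units.** The documents do not establish this. The stated time base points to 63 fixed days, on which no inflation occurs. *Total* can simply mean summed over three cycles, so it does not plainly contradict *standardized*. What remains is an ambiguity to close.

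**A reader might infer that stopping also inflates the AUC, or removes the weeks.** Stopping cannot add days. The weeks most likely come back through WOCF. They would vanish only if unscheduled assessments were not counted as missing.

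**A reader might take the 25% allowance as the share of patients who stop chemotherapy.** It is not. It builds on the pilot's total dropout of 22.41% and on COVID-19.

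**Cycle alignment is a legitimate choice.** This stands. Acupuncture sessions and the mESAS schedule also follow the cycle. On a calendar window, a delayed patient contributes less chemotherapy and fewer sessions than a patient treated on time. Replacing the cycle-aligned AUC outright would be a trade-off, not a plain correction.

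**Conclusion.** The concern holds for the collection of data and for the definition of the AUC. As scheduled, FACT-Ga ends with chemotherapy, and the lost weeks most likely enter the primary AUC at the patient's worst score. For one lost cycle this costs the affected patient 105 to 420 units, or 17% to 68% of the planned difference.

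That range assumes a worst score 5 to 20 points below the patient's mean, and that the patient would otherwise have stayed near that mean. If the patient truly deteriorated, the imputed value would be closer to the truth. The size and direction of any bias between arms cannot be derived, because no stopping or delay rates are given; the 2% to 14% shift is illustrative only.

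For delayed cycles, the likelier consequence is that the delay weeks are left out. Inflation is only a possibility that the wording leaves open. The stated sample size is not affected. The schedule should be changed because the remedy is cheap and has to be in place while patients are being followed.

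**What to change.** 1. **Collection.** In the FACT-Ga schedule under Secondary outcomes and in Table 1, state that weekly FACT-Ga continues to day 63 from day 1 of cycle 1, whether or not chemotherapy is delayed or stopped or acupuncture ends. Use these observed values in the AUC instead of imputing them.
2. **Definition.** Give one definition of the AUC with a fixed 63-day base, and use it under Primary outcome, Secondary outcomes and Sample size, so that a delay cannot add days. Say what *standardized* means, or drop the word.
3. **Analysis.** Report both a calendar-time AUC (days 0 to 63, actual assessment dates) and the cycle-aligned AUC. Name in advance which is primary and which is the sensitivity analysis.

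**Cost.** Patients whose chemotherapy is delayed or stopped fill in a few extra questionnaires. Assessments are planned at the sites' inpatient departments, and phone or WeChat contact is planned for reminders (Quality control), so remote completion off cycle would be a small new procedure. In the calendar-time AUC, weeks will not match cycle phase for delayed patients, which is why both versions are reported. The sample size does not change, and no rule on chemotherapy or acupuncture is touched.
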